## Abstract

**Background:**

Eating disorders (EDs) remain challenging to treat effectively, with low recovery percentages and high relapse rates. This study protocol explores autonomy-enhancing therapy as a therapeutic adjunct to existing day care treatment in the last phase of treatment. Autonomy-enhancing therapy is aimed at improving autonomy-connectedness: the capacity for self-steering while connected to others, which encompasses self-awareness, sensitivity to others, and the capacity for managing new situations. Higher autonomy-connectedness has been associated with improved ED recovery and lower relapse rates, yet little is known about the effectiveness of autonomy-enhancing therapy in ED populations.

**Objective:**

This study examines the effectiveness of autonomy-enhancing therapy in the last phase of a multidisciplinary day care program for anorexia and bulimia nervosa.

**Methods:**

A combined single-case experimental design and repeated measures design will be used, involving participants who are in the last phase of day care treatment for anorexia or bulimia nervosa (n=22-30). Participants will receive weekly autonomy-enhancing therapy sessions focused on personal autonomy-related goals and themed group discussions. The primary outcomes (ED symptoms and autonomy-connectedness) will be assessed weekly using the Eating Disorder Examination Questionnaire–Short (EDE-QS) and a short-term version of the Autonomy-Connectedness Scale (ACS-30-ST). Secondary outcomes (depression, anxiety, self-esteem, and quality of life) will be assessed every 3 months using the Symptom Checklist (SCL-90), Rosenberg Self-Esteem Scale (RSES), and World Health Organization Quality of Life–Brief Version (WHOQOL-BREF). Throughout the treatment, we expect improvements in autonomy-connectedness and a decrease in ED symptoms, with autonomy-connectedness mediating treatment success. Additionally, increased self-esteem and quality of life and reduced depression and anxiety are expected after treatment. Visual analysis of the single-case experimental design data and mixed models will be used to evaluate treatment effectiveness, with mediation analyses exploring the role of autonomy-connectedness.

**Results:**

Data collection started in March 2024. As of September 2026, 18 participants have completed the study, and 6 are enrolled. An additional 7 participants have been recruited. Data collection is expected to be finalized in February 2027; results are expected to be published in the second half of 2027.

**Conclusions:**

This study addresses the need for improved ED treatments by investigating autonomy-enhancing therapy as a potentially valuable adjunct to existing care. Targeting autonomy-connectedness may contribute to reductions in ED symptoms, as well as to broader psychological recovery. Strengths of this study include its practice-based design and the use of a single-case experimental design, allowing a detailed examination of treatment processes. Limitations include the absence of a control condition and the limited follow-up period, which may not fully capture relapse during the period of highest relapse risk. If promising, this study may provide a foundation for future larger-scale controlled studies on autonomy-enhancing therapy in ED treatment.

## Introduction

### Background

Eating disorders (ED) in adults are notoriously difficult to treat. Although guidelines recommend several well-established treatments [1], it remains unclear which of these is most effective, and no treatment for anorexia nervosa (AN) currently meets the highest level of evidence [2] (ie, level I evidence according to the Oxford Centre for Evidence-Based Medicine criteria [3]). Currently, only about 50% of patients with bulimia nervosa (BN) and 40% of individuals with AN fully recover after 5 years [4], with relapse rates between 22% and 51% [5]. The highest relapse risk occurs 4 to 6 months after treatment [4]. The debilitating nature of ED makes these high relapse and low recovery rates particularly concerning [6].

At the same time, there is increasing recognition that EDs involve more than eating and weight-related symptoms alone. Evidence suggests that disturbances in self-functioning and interpersonal functioning play an important role in the development and maintenance of these disorders [7]. Historically, EDs have been closely linked to disturbances in identity and the self [8]. Difficulties such as low awareness of needs [9] and poor self-concept clarity [10], paired with high self-criticism and self-objectification, may increase vulnerability to eating pathology by fostering reliance on external validation in defining identity and worth [9,11] and the need to control food and the body as a way to experience autonomy, competence, and identity [8].

Thus, improving treatment to aid transdiagnostic recovery, societal rehabilitation, and relapse prevention is crucial. Given the associations between autonomy-connectedness and ED symptoms and comorbidity, autonomy-connectedness could be a useful addition to therapy [12-14]. Autonomy-connectedness refers to the capacity to identify, express, and pursue one’s own needs, wishes, and values while maintaining meaningful and reciprocal relationships with others. It reflects both self-direction and interpersonal connectedness, capturing the degree to which individuals can identify and strive for their own needs, considering those of others. Autonomy-connectedness consists of 3 components: sensitivity to others’ wishes, needs, and opinions; self-awareness, the awareness of one’s own wishes, opinions, and needs and the capacity to express these in social interactions; and the capacity for managing new situations, understood as the inclination to explore, and feeling at ease in new situations [15]. Autonomy-connectedness is informed by attachment theory and neoanalytical object-relation theory on the development of gender identity [16], and it understands that healthy psychological functioning implies a strong self as well as strong connectedness to others [15]. Autonomy-connectedness deficits are an important underlying vulnerability factor for developing mental health problems [17].

Several considerations support the potential value of autonomy-connectedness: (1) autonomy-connectedness predicts ED recovery [12]; in a longitudinal study, recovered patients showed decreases in sensitivity to others and increases in the capacity for managing new situations compared with patients who did not recover; (2) autonomy-connectedness is transdiagnostic, which is relevant considering the high comorbidity in ED [18]; (3) autonomy-connectedness partly explains sex differences in ED symptom severity [13] and develops during the same life stages (puberty and young adulthood) in which EDs typically emerge [19], with the shift toward independence and separation contributing to sex-specific prevalence differences in mental health issues; (4) autonomy-connectedness promotes a healthy identity by addressing the ego-syntonic nature of EDs, which can contribute to high relapse rates due to strong identification with the disorder [20]; and (5) a well-founded autonomy-connectedness therapy protocol, autonomy-enhancing therapy, exists [21]. Each of these will be elaborated on in the following sections.

The first reason to include autonomy-connectedness in adult ED treatment is that it has been identified as one of the strongest predictors of recovery from ED after 1 year of treatment [12]. Kuijpers et al [12] found that patients who recovered initially had higher sensitivity to others and showed a significant decrease in sensitivity to others along with an increased capacity for managing new situations after treatment when compared with patients who did not recover. These findings indicate that recovered patients benefited from their ED treatment by gaining autonomy.

Second, autonomy-connectedness is a transdiagnostic construct associated with all major comorbidities typical of ED [18]. For example, autonomy-connectedness is linked to anxiety [14,22,23] and depression [24-29], which are characterized by high sensitivity to others paired with low self-awareness. Additionally, excessive sensitivity to others is linked to internalizing personality disorders, while low sensitivity to others and a high capacity for managing new situations are associated with antisocial personality disorder characteristics [30]. Comorbid diagnoses, particularly mood and anxiety disorders [31], may reinforce ED symptoms and can affect treatment efficacy [32]. Importantly, autonomy-enhancing therapy has already been shown to be similarly effective as group cognitive behavioral therapy in treating anxiety disorders and related comorbid symptoms [23]. Incorporating a transdiagnostic construct such as autonomy-connectedness in ED treatment may therefore not only support ED treatment but also enhance the likelihood of sustainable recovery through the concurrent treatment of comorbid conditions.

Third, autonomy-connectedness is an important factor in explaining observed sex differences in ED symptom severity. In a large, representative community sample, autonomy-connectedness differences between the sexes partially explained sex differences in ED symptom severity [13]. Men and women consistently differ in sensitivity to others, with women reporting much higher sensitivity to others than men [33]. These differences may stem from gendered attachment experiences, which in turn shape distinct adult identities and psychological vulnerabilities. Importantly, the development of autonomy-connectedness coincides with the life stage in which EDs typically emerge: puberty and young adulthood [19]. Adolescence marks the move toward changes in relationships with parents (growing independence), while adolescents’ relationships with peers become more and more important, which indicates that the “self” is still being developed. This is when the prevalence of anxiety, depression, and ED starts spiking in girls compared with boys [34], and the abovementioned differences in autonomy levels also emerge [33]. Interestingly, observed sex differences in ED symptom severity are substantially reduced when controlling for sex differences in autonomy-connectedness [13]. This suggests that autonomy-connectedness may partly account for sex differences in ED symptoms. These sex differences in autonomy-connectedness may arise from differing gendered attachment experiences for both sexes [8]. This finding suggests that it might not be solely “femaleness” that increases the likelihood of developing ED, but rather feminine attachment experiences.

Fourth, autonomy-connectedness relates to self-awareness and identity. ED, particularly AN, are often described as ego-syntonic phenomena (ie, the ED is seen as part of one’s true self, not an external illness that requires treatment) [20]. This ego-syntonic nature is suggested to contribute to high relapse rates [20]. Even if the current treatment effectively removes most ED symptoms, patients often struggle with identity and low empowerment afterwards, as the ED was intertwined with their sense of self [35]. Therefore, additional efforts are needed to rebuild a healthy self.

Finally, although a well-founded autonomy-connectedness therapy protocol, autonomy-enhancing therapy, exists [21], little is known about its effectiveness in ED treatment. Addressing this gap constitutes the need for the current study. For more details on autonomy-enhancing therapy, refer to the Methods section.

In summary, autonomy-connectedness appears to provide new insights into ED, and it is a promising and likely useful addition to ED treatment. Therefore, the study described in this protocol is aimed at testing the effectiveness and mechanisms of autonomy-enhancing therapy in the last phase of ED treatment for AN and BN.

### Hypotheses

Throughout autonomy-enhancing therapy, we expect (1) ED symptoms to decrease, (2) autonomy-connectedness to improve (ie, self-awareness and the capacity for managing new situations to increase, and sensitivity to others to decrease), and (3) autonomy-connectedness to mediate treatment success.

We will explore the differences between ED diagnoses (AN and BN) in relation to hypotheses 1 to 3.

Additionally, with respect to the secondary outcomes, we expect increased self-esteem and quality of life and reduced depression and anxiety at the posttreatment assessment compared with the pretreatment assessment.

## Methods

### Ethical Considerations

Ethics approval for the study protocol was obtained from the Medical Ethics Review Committee of VU Amsterdam (NL83503.018.23) and the internal research ethics committee of GGZ Oost Brabant. All participants received written and verbal information about the study and provided informed consent to participate. All participant data are being deidentified. Data collection takes place through ResearchManager EDC (ResearchManager), a secure program through which participants are assigned a unique participant number. Only the principal researcher has access to the key linking participant numbers to names and email addresses.

### Design

Two designs are combined: a single-case experimental design (SCED) and a repeated measures (RM) design. Given the vulnerable and highly specific population of patients with severe EDs, a SCED was considered more feasible and ethically appropriate than, for example, a randomized controlled trial, as it reduces the number of participants required and avoids withholding treatment from a control group.

A SCED multiple baseline design differentiates between time and intervention effects, with participants serving as their own controls. Experimental control is demonstrated when changes in outcome variables occur consistently after the introduction of the intervention across staggered baselines. Replication of this pattern across participants strengthens causal inference regarding intervention effects. The number of baseline measurements is randomized (ie, the number of measurements before the start of the intervention), varying from 5 to 8 weeks (ie, 5‐8 measuring points). Weekly measurements are taken for the duration of the assigned baseline plus the length of the intervention. The Eating Disorder Examination Questionnaire–Short (EDE-QS) [36] and the ACS-30-ST measure short-term ED symptoms and autonomy-connectedness characteristics, respectively.

The RM design assesses long-term ED symptoms and autonomy-connectedness characteristics, as well as depressive and anxiety symptoms, self-esteem, and quality of life, every 3 months at the beginning, middle, and end of the intervention, along with a 3-month follow-up (4 measurements). After treatment, participants will also be interviewed about their experiences with autonomy-enhancing therapy. The interviews are intended primarily to provide a richer understanding of participants’ questionnaire scores and changes over time, including participants’ experiences with the intervention, how they perceived changes in autonomy-connectedness, well-being, and ED recovery, and whether these experiences are reflected in quantitative assessments. In addition, the interviews will be used to explore the acceptability and feasibility of the intervention and to identify factors relevant to future implementation. As the qualitative component is exploratory and descriptive in nature, interview data will be reviewed and summarized to identify recurring experiences and implementation considerations rather than subjected to an in-depth qualitative analysis. For a study procedure flowchart, refer to Figure 1. The data will be analyzed using mixed models with an unstructured covariance matrix.

**Figure 1. F1:**
[figure not shown]
Study procedure flowchart. RM: repeated measures.

### Participants

Participants will be 22 to 30 patients (aged 18‐65 years) at the Center for Eating Disorders, GGZ Oost Brabant, Helmond, the Netherlands, in the last phase of multidisciplinary ED treatment, where treatment focuses on consolidating recovery, facilitating the transition to outpatient care or treatment completion, promoting self-management, and preventing relapse.

Prior to this last phase of treatment, participants will have completed 9 to 12 months of day care treatment for AN or BN, consisting of 2, 3, or 5 days of group therapy every week, including psychotherapy, sociotherapy, psychomotor therapy, drama therapy, and supported meals and snacks. All participants will have a BMI higher than 18.5 kg/m^2^.

All patients moving into the last phase of treatment are eligible for participation in this study. Inclusion and exclusion criteria for this study are therefore identical to the criteria for moving into the last phase of treatment. Eligibility for moving into the last phase of treatment is determined by the multidisciplinary treatment team. Patients enter this phase when ED symptoms are considered to be in remission at a behavioral level, allowing treatment to shift from symptom reduction toward maintaining recovery gains and preventing relapse. Main reasons for not progressing to the last phase include patients finding treatment closer to home, patients requiring specific care for posttraumatic stress disorder, autism, or personality disorders, or patients dropping out of treatment after failing to adhere to day care weight gain requirements.

### Procedures

All patients in day care ED treatment at GGZ Oost Brabant are informed about the study by the main practitioner and the principal investigator, both orally and in written form. Before deciding to participate, patients have opportunities to ask questions and have 2 weeks to consider participation. Those who agree to participate fill out an informed consent form on paper. Each set of 4 participants is randomly allocated without replacement to a baseline length of 5, 6, 7, or 8 weeks, using a predetermined random list of 150 numbers generated using statistical software by an independent person in the presence of the main investigator. To start participants on their baseline measurements on time, main practitioners are asked to estimate when patients are likely to move on to the last phase of treatment. When participants have started baseline measures but need more time in day care treatment, baseline measures are paused until they are close to moving on.

When participants have started baseline measures but choose not to continue into the last phase of treatment, their allocated baseline number is placed back on top of the list.

All questionnaires are answered digitally on any device. Weekly measures will take approximately 10 minutes; 3-monthly measures will take approximately 30 minutes. Questionnaire invitations as well as reminders are sent by email.

Posttreatment interviews will take place at the GGZ facility or online, conducted by the investigator and guided by a topic-list. Interviews are audio-recorded and later transcribed.

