### Intervention

Autonomy-enhancing therapy’s goal is to enhance autonomy-connectedness at behavioral, attitudinal, and emotional levels by working on personal, autonomy-related goals.

The investigational treatment, autonomy-enhancing therapy, consists of 15 weekly 2-hour group sessions, following the existing autonomy-enhancing therapy protocol [21]. The autonomy-enhancing therapy protocol prescribes a mindfulness exercise, space to share progress toward personal autonomy goals, and the appointment of a chairperson for each session who, with therapist support, keeps time. Each week features different autonomy-related themes (eg, relationships, boundaries, body and sexuality, and emotions), including psychoeducation, exercises, homework, and discussion of autonomy-related difficulties. Autonomy-enhancing therapy groups typically consist of 8 participants (range 4‐10).

The autonomy-enhancing therapy protocol has been slightly adjusted to fit the existing structure of the last phase of treatment in the Center for Eating Disorders, GGZ Oost-Brabant, Helmond. In this phase of treatment, participants are part of a group that follows several treatment modules together. Relapse prevention is covered in standard treatment, so introductory, relapse prevention, and midpoint evaluation sessions are omitted, leaving 12 sessions. Additionally, new members continuously join the group in the last phase of treatment, so patients start with whatever theme is planned for that week, ensuring that all themes are covered, even if the starting point varies. In the last phase of treatment, patients participate for a minimum 3 to maximum 6 months, with continuation decided after an evaluation at 3 months. Continuation or discharge is determined by main practitioners, guided by input from the treatment team. Participation in the intervention stops when individuals are discharged. After finishing their ED treatment, many patients proceed to other forms of treatment (eg, trauma treatment, treatment focused on personality disorders, or general psychological support).

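### The randomized baseline length appears to set how many measurements precede a clinically timed start, not when therapy starts, so consistency across staggered baselines is not sufficient proof of experimental control

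*Protocol article*

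**What the plan says.** Design section: "The number of baseline measurements is randomized (ie, the number of measurements before the start of the intervention", with 5 to 8 weekly points. Procedures section: "Each set of 4 participants is randomly allocated without replacement to a baseline length of 5, 6, 7, or 8 weeks".

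The Design section draws a causal inference from this: "A SCED multiple baseline design differentiates between time and intervention effects, with participants serving as their own controls", and "Experimental control is demonstrated when changes in outcome variables occur consistently after the introduction of the intervention across staggered baselines". It adds that replication across participants strengthens the inference.

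The start of therapy is described elsewhere. In Participants: "Eligibility for moving into the last phase of treatment is determined by the multidisciplinary treatment team"; the basis for entry is judged remission of eating disorder behavior. In Intervention, the therapy is embedded in the usual care of that last phase, and members join an ongoing group, "so patients start with whatever theme is planned for that week". That last quote concerns the order of themes. It shows that a patient can begin on joining the group, but not who sets the date.

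Procedures has two rules that link measuring to the move. The first is "To start participants on their baseline measurements on time, main practitioners are asked to estimate when patients are likely to move on". The second covers patients who need longer in day care: "baseline measures are paused until they are close to moving on".

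**The concern.** In a multiple baseline design with randomized lengths, the draw is useful because it moves the intervention. A participant who draws 8 begins therapy 3 weeks later than the same participant would have with a draw of 5. Change caused by the patient's own course then has no reason to line up with the therapy start, and replication of that alignment carries causal weight.

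If the date of therapy is set clinically and the baseline is fitted in before it, the draw moves only the first questionnaire. Whatever happens to patients at the transition then falls just after the boundary between baseline and therapy at every length. The pattern that the Design section would read as experimental control could arise with no therapy effect. The Design section prefers this design to a randomized trial on feasibility and ethical grounds, so what the stagger can show determines what the trial may conclude.

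**Working it through.** No figure in the article rests on this point, so there is none to reproduce. The check is structural, with a simulation for scale.

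**1. What the draw moves.** Let S be the date of entry to the last phase, L the drawn length (5 to 8 weeks) and B the date of the first measurement. Assume weekly spacing and no pause.
- *Counted forward:* B is fixed and therapy starts at B + L. Over L = 5 to 8 the start moves by 8 − 5 = 3 weeks.
- *Counted back:* S is fixed by the team and B = S − L. Therapy starts at B + L = S for every L, so the start moves by 0 weeks.

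**2. Which one the text describes.**

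| Element | Section | What sets it |
|---|---|---|
| Number of baseline points | Design, Procedures | The draw |
| Entry to last phase | Participants | Treatment team, on judged remission |
| Start of therapy | Intervention | Part of the last phase |
| Start of measuring | Procedures | Practitioner's estimate of the move date |
| Late move | Procedures | Measuring waits |

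Both timing rules adapt measuring to the move; neither adapts the move to the draw. A forward-counted design would need neither a predicted move date nor a pause when the patient stays longer. Counting back is therefore the natural reading.

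**3. Scale.** The simulations contain no therapy effect. Assumptions not taken from the article: 20 weekly points, SD 1, first-order autocorrelation 0.3, lengths allotted in sets of four, and a one-sided .05 randomization test over the four lengths. This test is not planned; it stands in for inference from the stagger. With 30 participants and an abrupt improvement at the transition, the false-positive rates were:

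| Change at transition | Counted back | Counted forward |
|---|---|---|
| None | 5% | 4% |
| Step of 0.5 SD | 59% | 6% |
| Step of 1 SD | 98% | 7% |
| Linear trend only, 0.05 SD/week | 4% | 3% |

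With 28 participants, counted back, the timing of the change was varied:

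| Change | False positives |
|---|---|
| 0.5 / 1 SD step at therapy start | 55% / 95% |
| Same steps, one week earlier | 11% / 20% |
| Same steps, two to four weeks earlier | 0–3% |
| Gradual 8-week change centered 0–4 weeks before start | 5–13% |

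The stagger thus fails for change that coincides with the transition. It still discriminates against abrupt change two or more weeks earlier and against a linear trend.

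**4. The planned model.** The primary test uses one treatment-versus-baseline dummy with time centered within each period. It compares period means and makes no use of the stagger. In an approximation (participant-level t test of the difference in phase means), a trend of 0.02 SD/week without therapy effect gave 51–54% false positives under either way of counting. The model therefore cannot supply the control that the stagger lacks.

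**The case against.** **Counting back is inferred.** This stands in part. The article never uses the words, the flowchart in Figure 1 is not shown, and nothing says what happens when a patient is ready before the baseline is complete. The statement that weekly measuring runs for the assigned baseline plus the intervention fits either reading. A reader might infer that therapy certainly starts at the same point whatever is drawn; the text does not go that far.

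**Not all confounding change is hidden.** This also stands. A reader might infer that the stagger gives no protection against maturation or time in care. That is too broad. Day care lasts 9 to 12 months, so change at a fixed time in care is not pinned to the therapy start. Improvement that leads the team to judge remission precedes entry and could appear in the baseline. The planned visual analysis looks at trend, level and immediacy and could reveal it.

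**The high error rates are a special case.** Correct. The 59% and 98% need an abrupt change in the very week therapy starts and come from a test that is not planned. They are not error rates of this trial. The obvious cause of such a change is the simultaneous switch to last-phase usual care, and counting forward would not separate that switch from the therapy.

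**Limitations are disclosed.** Only partly. The abstract names the lack of a control condition, and the Discussion concedes that concurrent usual care makes attribution difficult. Neither says that the stagger does not set the therapy start, and the Design section still offers the stagger as the source of control. The Discussion's praise of the multiple baseline design claims only insight into the treatment process, so little there needs correcting.

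**Conclusion.** The concern holds in limited form and should be fixed. As described, the draw determines how many weekly measurements precede a clinically timed entry. On the natural reading it displaces therapy by about 0 weeks relative to the patient's clinical course, against up to 3 weeks in a true stagger. Change that coincides with the transition would then satisfy the Design section's criterion at all four lengths with no therapy effect, so meeting that criterion is not sufficient proof of experimental control.

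This rests on two things: the inference that measuring is fitted to the transition, and the possibility of change at the transition itself. It does not show that the design is uninformative. Earlier change and steady trends could still be seen in the baseline, and the draw does vary the number of questionnaires already completed, which helps against repeated-measurement effects.

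**What to change.** 1. In Design, state that the randomized length sets the number of measurements before the transition and not the start of therapy. Drop consistency across staggered baselines as sufficient proof of experimental control, and describe results as within-person change around the transition.
2. Add this to the limitations in the Discussion. The sentence there on process insight needs at most a short qualifier.
3. If the allocated length does determine the start of therapy for some participants, say so, report for whom, and rest any causal statement based on the stagger on them.
4. Optionally, plot each series also by weeks since day-care admission, if those dates are available, so that readers can see whether change follows the therapy start or time in care.

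The cost is a few sentences and, if wanted, one more set of plots. No clinical rule changes. Data collection is projected to finish in February 2027, so this can be settled before the analysis. The real price is a weaker causal claim.
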